To date, no study has yet compared both treatment options in terms of biomechanical outcome with kinetic, kinematic changes, and compensation mechanisms.

The majority of earlier studies of syndesmosis fixation, which demonstrated the equality of both treatment options, used only standardized questionnaires and plain radiographs to assess syndesmosis reduction and clinical outcome.

Therefore, the purpose of this prospective randomized controlled single-center study was to assess the functional outcome namely by ankle range of motion as well as maximum ankle power as obtained via gait analysis and to rate the clinical and radiologic outcome by monitoring the stabilization of acute syndesmosis rupture with either a static implant (a 3.5-mm metallic screw through three cortices) or a dynamic device (TightRope®).

In this study, we expect that dynamic fixation would provide an equivalent or better clinical and radiologic outcome as well as a similar or better function of the ankle, i.e., larger range of ankle motion within the gait cycle and a larger maximum plantar flexion power at pre-swing. It can be assumed that when the maximum ankle performance normalizes, there is sufficient healing.

This study focuses mainly on the treatment of syndesmosis rupture, but it also aims to gain insights into patients’ satisfaction in correlation to functional outcome and surgical technique. Additionally, the study targets to show how risk factors, different therapeutic modalities, and/or treatment strategies influence this outcome. In future, the risk of long-term consequences and complications should be minimized by analyzing the new and already existing data, the clinical-functional follow-up examination, and the subjective result.

The study protocol for this study is described in the present manuscript.

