### Sample size calculation and statistical analyses

Formal sample size determination is not possible as potential effects are not yet known. Data from previous studies were utilized to determine the necessary sample size [23–25]. We plan a sample size of 25 patients, who will be treated with the cortical screw fixation and 25 patients, who will be treated with the dynamic TightRope® system within 2 years. The patients will be randomized to the two different treatment options. The randomization will be independent of the surgeon and the doctor who will do the examinations and the questionnaires.

The Shapiro-Wilk test will be used to check if our population is normally distributed. Standard unpaired Student’s *t* test to detect significant changes between the two groups will be conducted, if they are normally distributed. In contrast, possible differences for continuous data and scores between groups will be evaluated with the Wilcoxon *U* test, if no normal distribution exists.

The empirical distribution of continuous data and scores will be reported and calculated with means, standard deviation (SD), median, minimum, and maximum values and with absolute and relative frequencies for categoric data as well as unpaired *t*-test *p* values to depict a significant difference between the different groups. All descriptive analyses will be calculated for demographic data and for the dependent variables derived from the functional assessment, gait analyses results, and questionnaires of both groups.

An independent senior statistician of the Institute of Medical Biometry and Informatics of our university will perform the analysis. The intention-to-treat population will be used.

The analysis and illustrations will be carried out by use of SPSS version 25.0 for 135 Windows (IBM Corp., Armonk, New York, USA) and GraphPad Prism version 6.00 for Windows (GraphPad Software, San Diego, California, USA). For the representation of statistical relationships, the Pearson correlation coefficient will be used. The final details of the statistical analysis will be established in a statistical analysis plan, which will be completed before the closing of the database (before the end of data collection). A *p* value of ≤ .05 will be used to indicate statistical significance. Only a complete follow-up examination will be considered in the statistical analyses.

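### The Pearson coefficient is named without condition for relationships, while group comparisons of non-normal data have a rank alternative (minor, exploratory aim only)

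*Protocol article*

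**What the plan says.** Three statements in the protocol article, section 'Sample size calculation and statistical analyses', bear on this point.

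- Normality is checked: "The Shapiro-Wilk test will be used to check if our population is normally distributed".
- Group comparisons use a t test under normality. Otherwise, "possible differences for continuous data and scores between groups will be evaluated with the Wilcoxon *U* test, if no normal distribution exists".
- For associations there is one unconditional rule: "For the representation of statistical relationships, the Pearson correlation coefficient will be used".

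No rank correlation is named anywhere in the article. The use of correlation that can be traced is in the Background, where a subsidiary aim is to look at patients' satisfaction "in correlation to functional outcome and surgical technique". The section also sets a general significance rule ("A *p* value of ≤ .05 will be used to indicate statistical significance") and leaves final analysis details to a statistical analysis plan, which is not shown.

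**The concern.** The section allows for data that are not normal and provides a rank method for one use of them. It then fixes a linear coefficient for another use of what may be the same variables, with no alternative. This is a stated method that does not follow the section's own logic, which is different from a detail left open.

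The recorded variables include some for which a linear coefficient is a doubtful sole tool. The secondary outcomes list time to recovery and return to work, and such times may be right-skewed. The MRI appearance is recorded in ordered grades, from unaffected to complete tear. The protocol does not say which variables will be correlated, so these are candidates only.

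At stake is whether a real monotone relation in skewed data would be described as weaker than it is, or overlooked.

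**Working it through.** **No figure to reproduce.** The protocol gives no expected correlation and no power or precision target for correlations; it says "Formal sample size determination is not possible as potential effects are not yet known".

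**Inputs.**
- Sample size: 25 + 25 = 50 ("We plan a sample size of 25 patients, who will be treated with the cortical screw fixation and 25 patients").
- Significance level: 0.05 from the protocol; two-sided is an assumption, since sidedness is not stated.
- Latent correlation ρ: 0.4, assumed, with 0.5 as a check. For scale, the correlation detectable with 80% power at n = 50 under normality is, by Fisher's z, (1.96 + 0.84)/√(50 − 3) = 0.409, and tanh(0.409) = 0.39.
- Shapes: normal, lognormal (SD σ on the log scale), and bounded scores with a ceiling or floor. All are assumptions.

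**Step 1: what skew does to the coefficient.** Take bivariate normal data with ρ = 0.4 and exponentiate with σ = 1.
- Pearson, both variables lognormal: (e^(ρσ²) − 1)/(e^(σ²) − 1) = (1.492 − 1)/(2.718 − 1) = 0.286.
- Pearson, one variable lognormal: ρσ/√(e^(σ²) − 1) = 0.4/1.311 = 0.305.
- Spearman, all of these cases: (6/π)·arcsin(ρ/2) = 1.910 × 0.2014 = 0.385, because ranks do not change under an increasing transformation.

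The simulated means at n = 50 were 0.31 and 0.33 for Pearson, somewhat above these population values, and 0.38 for Spearman in both cases.

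**Step 2: power at n = 50, ρ = 0.4** (5,000 runs per row; Monte Carlo standard error of each figure at most √(0.25/5000) = 0.7 points).

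| Shape | Pearson | Spearman |
|---|---|---|
| Both normal | 85% | 80% |
| One lognormal, σ = 1 | 67% | 78% |
| One lognormal, σ = 1.5 | 54% | 79% |
| Both lognormal, same direction | 53% | 79% |
| Both lognormal, opposite direction | 32% | 77% |
| Normal against ceiling score | 80% | 78% |
| Ceiling score against floor pain scale | 74% | 72% |

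A separate simulation (3,000 runs per scenario) gave 55% against 80% with both variables lognormal, 67% against 79% with one, and 69% against 71% with ceilings only. The opposite-skew row is an extreme case from one simulation only and is left out of the range used in the conclusion.

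**Step 3: false positives.** With ρ = 0 at n = 50, both coefficients rejected in 4.4% to 5.2% of runs in every shape.

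**Step 4: sensitivity.** With both variables lognormal (σ = 1), power was 74% against 94% at ρ = 0.5 and n = 50. At ρ = 0.4 it was 49% against 68% with n = 40, and 37% against 47% with n = 25. The gap persists in smaller samples.

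**Step 5: what a switch based on Shapiro-Wilk would do.** Normality of at least one of the two variables was rejected in more than 99% of the ceiling and floor samples at n = 50, although Pearson loses nothing there. It was rejected in about 10% of samples when both were truly normal, as expected from two tests at 5%: 1 − 0.95² = 0.0975.

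**The case against.** The strongest reply is that this is a matter for the analysis plan. The sentence that follows the Pearson rule defers final details to it, and choosing a coefficient by variable type is ordinary content there. This stands in part: nothing prevents the analysis plan from adding the alternative. But the protocol has not left the coefficient open. It names one without condition, and an analysis plan that follows it inherits the mismatch.

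The second reply is that the loss is not shown for the main instruments. OMAS, FAOS, SF-12 and VAS pain are bounded scores, and with a ceiling or floor alone the two coefficients are equal within about 2 points. This stands. The power loss requires strong skew, which the protocol neither reports nor predicts; the rank rule is conditional ("test, if no normal distribution exists").

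Three stronger readings are tempting and are not supported.

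- *Correlations will be tested.* A reader might infer this from the general significance rule. The sentence itself speaks only of representing relationships. The power figures therefore serve to show the size of the attenuation.
- *Pearson would create spurious relations in skewed data.* The false-positive rate stayed near 5% in every scenario with independent variables.
- *A coefficient pooled over both arms would confuse treatment differences with a link between satisfaction and function.* The protocol does not say whether correlations are pooled, computed by arm or adjusted, so this would criticise an analysis that it does not describe.

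**Conclusion.** The point holds as a minor inconsistency. Pearson is fixed for all relationships, while the same section gives group comparisons a rank method for non-normal data. If a correlated variable is strongly right-skewed, Pearson understates a monotone relation (mean coefficient about 0.29 to 0.33 instead of 0.40) and has about 53% to 67% power where Spearman has 78% to 80%. This rests on n = 50, an assumed latent correlation of 0.4 and assumed lognormal shapes. It does not extend to every non-normal variable: for bounded scores with a ceiling or floor there is no meaningful difference.

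The consequence is confined to a subsidiary aim, mentioned in the Background of a pilot study that also sets out to generate hypotheses. No comparison of the two fixation methods depends on it.

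**What to change.** Replace the sentence on the Pearson coefficient by:

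> Relationships will be described with the Pearson coefficient where both variables are approximately normal, and with the Spearman rank coefficient where either is ordinal or not normally distributed, each with a 95% confidence interval.

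The cost is one sentence. The downside is small: for bounded scores with a ceiling or floor the change brings little or no gain and may lose about 2 points of power. Where both variables are approximately normal, Pearson is kept, so the roughly 5 points that Spearman would give up there (85% against 80%) are largely avoided.

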**Table 1 Tab1:**
[figure not shown]
Overview of clinical and radiologic follow-up. *CT* computed tomography, *MRI* magnetic resonance imaging, *SF-12* 12-item Short Form Health Survey, *VAS pain* visual analog scale for pain

MRI images will be assessed by a senior radiologist for degenerative changes of the tibiotalar joint and the syndesmosis structure (unaffected, hyperintense signal alteration on T2, partial tear, complete tear), widening, and calcification. By using questionnaires preoperatively and postoperatively after 6 weeks and 3, 6, and 12 months during the appointments, patients can provide information on pain, mobility of foot and ankle, and quality of life (SF-12) [19] during the course of treatment. General patient data, including age, profession, body mass index (BMI), risk factors, medication, concomitant diseases, previous surgeries, and details of the accident, will be documented preoperatively.

At 25 weeks postoperatively, patients also receive a gait analysis and MRI is performed to assess motion anomalies and the healing process of the syndesmosis.

The planned study will run over 2 years. Patients will be admitted over a period of 1 year. Each patient will be treated and followed-up over a 12-month period.

All data will be stored and monitored using pseudonyms. The data of all patients will be analyzed statistically and compared at the end of the 2 years (Table 1).

Furthermore, all data of the participating patients will be carefully assessed, and all adverse events and complications of the treatment will be reported at the end of this trial. The harms will be categorized according to their degree of severity in either serious or non-serious.

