### Primary outcome measures

The primary endpoint of this study is a successful healing of the syndesmosis 6 months after surgery by evaluation of MRIs of the ankle [26]. MRI scanning in the plane of the syndesmotic ligaments is the investigation of choice to evaluate syndesmosis healing. MRI images will be evaluated for degenerative changes of the cartilage of the ankle, appearance (unaffected, hyperintense signal alteration on T2, partial/complete tear), widening, and calcification of the syndesmosis. If these evaluations are ordinary, successful healing can be assumed and will be classified as healed by a senior radiologist.

Another primary outcome measurement of this study is the gait analysis 6 months postoperatively to detect biomechanical differences between both treatment groups.

Due to the pilot study character, it remains to be clarified which are the most suitable parameters to depict potential effects and differences.

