### Secondary outcome measures

Secondary endpoints and measurements will be recorded 6 weeks and 3, 6 and 12 months postoperatively. The measurements include different questionnaires mentioned above with subjective evaluation of the quality of life (assessed by the 12-item Short Form health survey [SF-12] questionnaire) [19] and pain (visual analog scale [VAS]). In addition, a self-designed questionnaire as well as the “Score of Olerud und Molander (OMAS)” [20] and “Foot and ankle outcome score (FAOS)” [27] will be used to evaluate the range of motion, deficits in daily life, symptoms after ankle fractures and after surgical treatment, and socioeconomic factors (period of time, returning back to work, and time of recovery).

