### Trial status

The RCT trial is ongoing (study protocol version 1.0 02.08.2017, S-454/2017), patient recruitment, and surgical treatment began in December 2017. Recruitment is expected to be completed in December 2019. The follow-up is conducted over a 12-month period for each patient included. Data analysis will only be performed after complete 1-year follow-up. Thereafter, the final results will be published.

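### A complete-follow-up restriction sits beside the intention-to-treat statement; its wording is ambiguous, and on either reading it discards usable data and risks attrition bias

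*Protocol article*

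**What the plan says.** The section on sample size and statistical analyses first fixes the population: "The intention-to-treat population will be used". The following paragraph ends with a restriction: "Only a complete follow-up examination will be considered in the statistical analyses". Nothing limits that restriction to secondary outcomes or labels it a sensitivity analysis.

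Two other places bear on who is analysed. The Follow-up section, under Table 1, says: "The data of all patients will be analyzed statistically and compared at the end of the 2 years". The section on criteria for termination allows a withdrawn participant's recorded data to stay in the evaluation with consent, or to be destroyed on request.

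Both primary outcomes are measured at 6 months. One is "successful healing of the syndesmosis 6 months after surgery by evaluation of MRIs of the ankle". For the other: "Another primary outcome measurement of this study is the gait analysis 6 months postoperatively". The visit schedule runs longer: "Secondary endpoints and measurements will be recorded 6 weeks and 3, 6 and 12 months postoperatively".

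The Randomization section separately removes from the final analysis randomised patients in whom no acute rupture needing stabilisation is found during surgery.

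**The concern.** Intention-to-treat leads a reader to expect every randomised patient to be compared in the assigned arm. A restriction to complete follow-up narrows that set by something that happens after randomisation.

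On the full-schedule reading, a missed 6-week, 3-month or 12-month visit removes a primary result that was validly obtained at 6 months. Two things are then at stake:

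- **Precision.** The trial plans 25 patients per arm with no stated allowance for dropout, so every avoidable exclusion counts.
- **Comparability.** Completing a year of visits may depend on how the patient is doing, and possibly on the arm. Only the screw arm has a planned second operation between weeks 6 and 8, and the article says that patients can no longer be blinded from that point. If loss depends on both arm and outcome, the completers are no longer the randomised groups.

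The planned tests are ordinary difference tests, while the article's alternative hypothesis is equality of the two treatments. Lost precision makes a non-significant result more likely, and such a result could be misread as support for equality.

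**Working it through.** **1. The two readings side by side**

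- *Full schedule.* The Trial status section uses similar words for the whole year of follow-up: "Data analysis will only be performed after complete 1-year follow-up". Read this way, the patient must attend all four visits (6 weeks, 3, 6 and 12 months) to be analysed at all.
- *Single examination.* The Objectives and hypotheses section uses the term follow-up examination for the 6-month visit. Read this way, a patient with a complete 6-month visit stays in whatever else was missed, but a patient with the MRI and no gait analysis (or the reverse) loses the measurement that was obtained.

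Both readings select on completeness after randomisation.

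**2. Inputs for the size**

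From the article: 25 per arm, 50 in total; 1:1 allocation; significance level 0.05; four follow-up visits; primary outcomes at the third. Assumed, because the article does not give them: a two-sided test, 80% power, and a proportion m missed per visit. The planned 25 per arm cannot be reproduced, since the article states no effect size, SD, power or dropout rate.

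**3. Patients kept, full-schedule reading, misses independent between visits**

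With 6-month data: 50 × (1 − m). Complete at all four visits: 50 × (1 − m)^4.

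| m (assumed) | With 6-month data | All four visits |
|---|---|---|
| 5% | 50 × 0.95 = 47.5 | 50 × 0.95^4 = 40.7 |
| 10% | 50 × 0.90 = 45.0 | 50 × 0.90^4 = 32.8 |
| 15% | 50 × 0.85 = 42.5 | 50 × 0.85^4 = 26.1 |

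**4. Detectable difference for a continuous gait parameter**

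Noncentral t, two equal arms of n, 2n − 2 degrees of freedom, noncentrality d × √(n/2); d is solved for 80% power.

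- No loss, n = 25: 0.81 SD.
- m = 5%: 0.83 SD with all 6-month data (n = 23.75), 0.90 SD with completers only (n = 20.4). The restriction costs about 0.07 SD.
- m = 10%: 0.86 SD (n = 22.5) against 1.01 SD (n = 16.4), a cost of about 0.15 SD.

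The comparator is the number with 6-month data, not 25, because no analysis rule recovers a 6-month measurement that was never made. These figures do not apply to MRI healing, which is classified as healed or not.

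**5. Monotone dropout instead**

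If patients who miss a visit never return, the only extra loss is those who leave between 6 and 12 months. With 5% leaving before each visit, 50 × 0.95^3 = 42.9 have 6-month data and 50 × 0.95^4 = 40.7 are complete, so the restriction costs about 2 patients.

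**6. Bias, illustration with assumed rates**

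Suppose true healing is 80% in both arms and one arm loses 5% of healed and 30% of unhealed patients. Among those remaining, healing is 0.80 × 0.95 / (0.80 × 0.95 + 0.20 × 0.70) = 0.76 / 0.90 = 84.4%, which is 4.4 points too high. If loss is 10% in both healed and unhealed patients, the rate stays at 80% and only precision suffers.

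**The case against.** The best defence is that the sentence speaks of one examination, not of a schedule, and that the article elsewhere uses the term for the 6-month visit. On that reading the primary comparison keeps everyone with a complete 6-month visit. The Trial status sentence governs when analysis starts, not who enters it. This stands, and it means that the loss of patients with valid 6-month data is one reading rather than a certainty. It does not clear the sentence: the narrower reading is still a complete-case restriction, and an analyst cannot tell which is meant.

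It can also be said that intention-to-treat fixes the arm in which a patient is counted, while use of observed data is a missing-data choice. That is fair. A reader might infer that the two sentences are logically incompatible, but a complete-case analysis by assigned arm is possible. It is a departure from full intention-to-treat that the article does not acknowledge.

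Three further inferences are tempting and unsupported:

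- *That bias will occur.* The article gives no dropout rate and no evidence that loss depends on arm or outcome. The visits are routine care, which may help attendance.
- *That the loss is as large as the independent-miss figures.* Independence over four visits is close to the worst case.
- *That an analysis at 2 years would find only about half the patients with 12-month data.* That joins the accrual period of one section to the analysis date of another. The Follow-up section is consistent in itself (1 year of accrual plus 1 year of follow-up), and the Trial status section rules out analysis before 1-year follow-up is complete.

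Finally, this is a hypothesis-generating pilot, and the details of the analysis are left to an SAP. That limits the consequences. It does not answer the point, because the article states a rule and the SAP would inherit two instructions that pull apart.

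**Conclusion.** The point holds in a limited form. The article states a complete-case restriction that conflicts with its declared population and with its statement that all patients' data are analysed, and the wording leaves open how far the restriction reaches.

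On the full-schedule reading, with an assumed 5% missed per visit and independence, it removes about 7 of the 47 to 48 patients with 6-month data and raises the detectable gait difference from 0.83 to 0.90 SD. Under monotone dropout at the same rate the loss is about 2 patients. On the single-examination reading the loss is confined to partial visits and cannot be sized from the article. Attrition bias is possible, not shown.

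The accrual and duration statements also disagree, but that is a separate inconsistency and does not enlarge this one.

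**What to change.** Replace the complete-follow-up sentence with wording to this effect: *All randomised patients are analysed in their assigned arm. Each 6-month primary outcome uses every patient with that measurement, whatever the attendance at other visits. Questionnaires use all available visits. An analysis of patients with complete follow-up is a sensitivity analysis.* Data destroyed at a participant's request remain an unavoidable gap and should be counted and reported. The method for missing values can stay with the SAP.

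In the same edit, state the Randomization section's exclusion (no acute rupture found during surgery) as a defined exception to intention-to-treat, or keep those patients in.

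Separately, reconcile the timelines. The Follow-up section has 1 year of accrual and a 2-year study. The Trial status section has recruitment from December 2017 and says "Recruitment is expected to be completed in December 2019"; adding 12 months of follow-up leads to December 2020.

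The cost is rewording and slightly more analysis work, with no added patients or visits. The change should be made before the database is closed.
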